### Interventions

#### Breaking free online health and justice

BFO is an online treatment program for substance-involved offenders. Clinical content of BFO has been informed by the available evidence-base around effective biopsychosocial and behavioral intervention approaches for addressing drug and alcohol misuse (National Treatment Agency for Substance Misuse 2006a, b; NICE 2007, 2011, 2012), including cognitive-behavioral principles (Beck 1993; Beck et al. 2011), and other approaches including mindfulness-based relapse prevention (Marlatt et al. 2010; Marlatt and Donovan 2005).

When an individual first uses BFO, they complete a psychometric assessment developed by the authors, the ‘Recovery Progression Measure’ (RPM: Elison et al. 2016a; 2017b, which is contained within the program. The RPM measures baseline levels of functioning, and treatment-related changes in functioning, across six domains; ‘negative thoughts’, ‘emotional impact’, ‘unhelpful behaviors’, ‘difficult situations’, ‘physical sensations’, and ‘lifestyle’. Data generated via completion of the RPM is then utilized by the BFO program to populate a visual depiction of a six-domain biopsychosocial model, the ‘Lifestyle Balance Model’ (LBM: Davies et al. 2015). The LBM forms the theoretical underpinnings of the program and is based on the five-factor model used in cognitive behavioral therapy (Greenberger and Padesky 1995; Williams and Chellingsworth 2010). The LBM (see Fig. 1) acts as a clinical formulation to help the user understand the domains of their functioning that may be implicated in their substance misuse.

**Fig. 1 Fig1:**
[figure not shown]
The Lifestyle Balance Model

Based on RPM scores, each of the six domains of the visual depiction of the LBM are colored either green, amber or red. This ‘traffic light’ system indicate respectively, ‘little’, ‘moderate’ or ‘significant’ impairment in each of the six domains. Tailored advice then guides the user to concentrate on completing intervention strategies contained in the program that are aligned to domains of functioning in the LBM where they may be experiencing the greatest levels of impairment (amber and red domains of the LBM). However, users are also encouraged to complete and interventions within green areas to help build long-term resilience.

Table 1 provides an overview of the clinical content of BFO and the theoretical underpinnings of individual intervention strategies within the program. Table 1 maps the clinical content of BFO onto individual behavior change techniques (BCTs) from the BCT taxonomy (V1) (Dugdale et al. 2016b). The BCT taxonomy (V1) provides a standardized means of describing the clinical content of complex behavioral change interventions (Michie et al. 2011).

**Table 1 Tab1:** Breaking Free Online content

Strategies included in Breaking Free Online	Description of strategy	Therapeutic approaches underpinning strategies	BCT taxonomy (V1) techniques (number in taxonomy)
Lifestyle balance model (individualized diagram)	Generic formulation; Idiosyncratic formulation; Personalized feedback; Case formulation – understand the links between situations, thoughts, emotions, behaviors, physical sensations and lifestyle	Node-link mapping (International Treatment Effectiveness Program (ITEP); Cognitive-behavioral therapy (CBT)	Information about antecedents (4.2); Information about health consequences (5.1); Salience of consequences (5.2); Information about social and environmental consequences (5.3); Information about emotional consequences (5.6)
Understanding your difficult situations	Assessment; Self-monitoring; Standardized measures; Psycho-education on impact of problematic situations; Intervention to help people in distress access support	All structured therapeutic approaches; Psycho-education; Guided self-help	Social support (unspecified) (3.1); Reduce negative emotions (11.2)
Managing your risky situations: Recognize– avoid–cope	Recognize–avoid–cope; Relapse prevention for coping with environmental/situational/emotional triggers; Creating action plans on how to avoid or cope in high risk situations	Relapse prevention; Refusal skills	Problem solving (1.2); Action planning (1.4); Instruction on how to perform a behavior (4.1); Behavioral practice/rehearsal (8.1); Behaviour substitution (8.2); Avoidance/reducing exposure to cues for the behavior (12.3); Goal setting (behavior) (1.1); Problem solving (1.2); Action planning (1.4)
Understanding your negative thoughts	Psycho-education on impact on negative thoughts	Psycho-education; Guided self-help	Information about antecedents (4.2); Information about health consequences (5.1); Salience of consequences (5.2); Information about social and environmental consequences (5.3); Information about emotional consequences (5.6)
Escaping your mind traps	Mind traps; Cognitive restructuring; Challenge thoughts that may be unhelpful	International Treatment Effectiveness Program (ITEP); Cognitive-behavioral therapy (CBT)	Re-attribution (4.3); Framing-reframing (13.2)
Understanding your emotions	Psycho-education on impact on emotions	Psycho-education; Guided self-help	Information about antecedents (4.2); Information about health consequences (5.1); Salience of consequences (5.2); Information about social and environmental consequences (5.3); Information about emotional consequences (5.6)
Shifting your focus	Attention narrowing; Attention switching; Emotional regulation; Recognize/understand/normalize emotions; Developing more appropriate coping strategies	Coping strategy enhancement (CSE); Mindfulness-based cognitive therapy	Information about emotional consequences (5.6); Behavioral practice/rehearsal (8.1); Reduce negative emotions (11.2); Problem solving (1.2); Social support (unspecified) (3.1); Behavioral practice/rehearsal (8.1); Distraction (12.4)
Understanding your physical sensations	Psycho-education on impact of physical sensations	Psycho-education; Guided self-help	Information about antecedents (4.2); Information about health consequences (5.1); Salience of consequences (5.2); Information about social and environmental consequences (5.3); Information about emotional consequences (5.6)
Surfing your cravings and urges	Urge surfing; Body scanning; Relapse prevention-based techniques	Mindfulness-based cognitive therapy	Instruction on how to perform a behavior (4.1); Behavioral practice/rehearsal (8.1); Reduce negative emotions (11.2)
Understanding your unhelpful behaviors	Psycho-education on impact of destructive behaviors	Psycho-education; Guided self-help	Information about antecedents (4.2); Information about health consequences (5.1); Salience of consequences (5.2); Information about social and environmental consequences (5.3); Information about emotional consequences (5.6)
Planning your time positively	Activity scheduling; Behavioral activation; Encourage new behaviors via positive feedback; Increase activity to increase energy levels and relieve boredom	Cognitive-behavioral therapy (CBT)	Non-specific reward (10.3); Non-specific incentive (10.6); Reward approximation (14.4); Rewarding completion (14.5); Goal setting (behavior) (1.1); Action planning (1.4)
Understanding your lifestyle	Psycho-education on impact of lifestyle; Creating SMART goals for recovery	Psycho-education; Guided self-help	Goal setting (behavior) (1.1); Problem solving (1.2); Goal setting (outcome) (1.3); Action planning (1.4)
Achieving your life goals	Goal-setting Increase treatment engagement and retention. Increase readiness to change behavior	Motivational enhancement therapy (MET); Implementation intentions	Non-specific reward (10.3); Focus on past success (15.3); Action planning (1.4)
Progress check	Monitor behavior to provide feedback about progress towards goals; Encourage new behaviors via positive feedback	Self-monitoring	Self-monitoring of behavior (2.3); Feedback on outcome(s) of behavior (2.7)
Information on alcohol and drugs	Psycho-education on effects of alcohol and drugs; Reduce negative or fatal consequences of substance using behaviors	Harm reduction; Psycho-education	Information about health consequences (5.1); Salience of consequences (5.2); Behaviour substitution (8.2); Habit reversal (8.4)

The BFO program has been designed to be used by individuals as either a stand-alone or adjunct treatment program alongside standard treatment, and as either self-help or as CAT with support by practitioners, keyworkers, peer-mentors or other supporters. However, in this study BFO will be delivered as a supplement to standard treatment. Consultation with HMPPS has ensured that all intervention strategies in the program are appropriate for the prison setting and comply with HMPPS quality assurance, security and information assurance processes. For this study, the BFO program will be comprised of 8 sessions which will be run over 4-weeks, with two sessions held each week.

### Standard treatment

Both study groups will receive standard treatment as part of the study design. It is expected that there will be a degree of heterogeneity within both the BFO and control groups in terms of the ‘standard treatment’ each participant receives. Information regarding the specific standard treatments each participant receives will be collected, including the specific standard treatments each participant receives, the number of sessions completed, what kind of practitioner has delivered it, and also the medications each participant may have been prescribed during the course of the study (see Additional file 1: Appendix B). These data will allow comparisons to be made between different control treatments.

In terms of the psychosocial and behavioral support available in the participating prison, low-intensity group-based interventions are usually delivered by key-workers in alcohol and drug misuse services and include techniques such as motivational interviewing and contingency management. These group-based interventions will be delivered with groups of participants that are of a similar size to the group sessions of BFO, i.e. groups of 10 participants. In order to avoid violation of the stable unit treatment value assumption, participants in the BFO group will receive their group-based standard treatment in groups that are run separately from the group-based standard treatments the control group receive.

More formal psychological therapies are usually delivered by specialist psychological therapists through CBT based interventions and are delivered on a one-to-one basis. All standard treatment sessions have a duration range of 30–60 min and take place once or twice a week for a period of approximately 4–12 weeks. The number of interventions each participant will receive may vary. During treatment concomitant alcohol and drug/s use may be permitted, as well as any prescribed medication (detoxification included).

### Procedure

Site investigators from the research team will work with the support of members of the team of substance misuse practitioners working in the prison to inform potential participants of the study. Site investigators will be responsible for completing screening, consent and randomization. Site investigators and practitioners will be responsible for conducting baseline and 4-week post-baseline assessments. Practitioners will be responsible for delivering both BFO and the standard treatments received by the two study groups. Site investigators will be responsible for conducting 3- and 6-month follow-up assessments. All site investigators and practitioners have been vetted and security cleared to work in prisons by HMPPS and have enhanced clearance via the UK Government Disclosure Barring Service. The site investigators have trained all participating practitioners in delivering BFO as CAT and have also conducted training around RCT methodology. All practitioners are trained and experienced facilitators of structured substance misuse interventions. Both site investigators and practitioners have received training in ethics and confidentiality issues when working with offenders in secure settings.

All prospective participants that potentially meet the study criteria will be informed of the study’s objectives and requirements using the Participant Information Sheet and Informed Consent Form before any screening procedures are performed. If willing to participate in the study, participants will be requested to provide written consent after being given sufficient time to consider their participation and having had the opportunity to ask for further details. During the informed consent procedure, participants will be provided with information about the fact they can withdrawal from the study at any time without giving a reason, and without their withdrawal affecting their recovery and rehabilitation support. Additionally, they will be assured that when their data are collected, no identifiable information can be traced back to them, and that their data will be fully anonymized.

The Informed Consent Form will be signed and dated by both the participant and the site investigator, and the participant’s preferred mode of contact (e.g. telephone, email etc.) and contact details for the completion of follow-up assessments will also be noted at this point. The participant will be provided with a copy of the signed consent form and the Participant Information Sheet. The original consent forms will be retained in a secure storage facility separately from source data to protect against breach of privacy and participant anonymity.

If written consent is given, each participant will then be screened for eligibility by the site investigator before then being randomized to either the BFO or control group. Randomization will occur at the level of the individual participants, with participants being assigned to one of the study groups following the generation of a random allocation sequence via the *Research Randomizer* (from the Social Psychology Network- Urbaniak and Plous 2011). Sequentially-numbered opaque sealed envelopes containing the treatment group that the participant will be allocated to will be delivered to the research site prior to commencement of the study. The participant number will be determined according to the order of enrolment in the study. The site investigator will assign and open one sealed envelope per participant. A screening log, including the participant number and treatment group assigned by randomization and any subsequent reason/s for exclusion from the study (if applicable), will then be completed by the site investigator.

No longer than 2-weeks after being randomized and completing the eligibility screening, both study groups will complete a battery of assessments to collect data around primary and secondary outcomes and demographic information including age and ethnicity. This battery of assessment will be delivered digitally via desktop computers within the prison IT suites. The assessment for the BFO group will be completed within the BFO program. The control group will complete the measures via a specially developed digital assessment platform which will deliver the same assessment that is included in the BFO program, but without providing access to any of the digital intervention content provided by BFO.

Study groups will then complete a period of 4-weeks of substance misuse treatment, of either i) BFO plus standard treatment, or ii) standard treatment only. For the BFO group, the 4-week intervention will be delivered to groups of approximately 10 participants at a time, so it is estimated that approximately 6–8 groups will need to run successively to achieve the sample size required, in order to account for some attrition between baseline and 4-week post-treatment assessments. BFO group participants will receive two sessions of BFO each week, alongside any standard treatment they may be engaging with.

Online access to the BFO program is granted via the activation of an access code given to the participant at the alcohol and drug misuse service by authorized practitioners. To activate the access card and create a personal account, the participant must enter a username and password of his choice along with the access code. The practitioners will be able to assist with the online access if required. The participants must also agree to the Terms & Conditions of using BFO, which are in accordance with the Participant Information Sheet and Informed Consent Form and conform to the European Union General Data Protection Regulation around the use of digitally captured personal data. The practitioners must ensure that they log out of BFO at the end of each treatment session to protect the confidentiality of the data.

Procedures to enhance retention of participants during the 4-week treatment period will include practitioners providing ongoing support during weekly key-working sessions, which all offenders in the prison will routinely receive during the standard substance misuse treatment. When participants do dropout of the study, new participants will be recruited and randomized to replace dropouts, in order to ensure the required sample size of 120 participants (60 per group) complete the 4-week treatment period and provide post-treatment data. However, in line with ITT principles, all randomized participants, including dropouts, will be included in the final analyses (see ‘Data Analysis’ section). After completion of the 4-week treatment period, participants in both groups will complete the same battery of digital psychometric assessments on the prison desktop computers.

Follow-up assessments will then also be completed at 3- and 6-months post-treatment with all participants. Follow-up assessments may be completed either in the community if offenders have been released, or in prison if they are still serving their sentence. The site investigators will work with the practitioners delivering both BFO and standard treatments to determine which participants have been released back to the community since completing their 4-week treatment period, and which participants are still serving their sentence in the participating prison. Additionally, those participants who have been transferred to a different prison will also be identified.

Depending on participants’ preference, the site investigators will contact all participants who have been released back to the community via telephone or email, and their assessment will be completed either over the phone, or via a link to an online version of the assessment. The preferred contact details for each participant that were collected at the time of consent and randomization will be used. For those participants who are still serving a prison sentence, or have been reconvicted and are serving a new sentence, or have been transferred to a different prison, they will be visited by the site investigator at their current prison and their follow-up assessment will be completed there.

By following the procedure described above, each participant will take part in the study for a total of approximately 7-months, including 4-weeks of treatment and 3- and 6-month follow-up assessments. It is likely that the study will run for a total of approximately 18-months, which will include enough time for recruitment, running enough successive 4-week long BFO groups to achieve the required sample size, and completion of all 3- and 6-month follow-up assessments.

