Another limitation lies in the fact that the level of randomization is at the level of individual offenders, which means that intervention group participants and control group participants will have the opportunity to interact with one another within the prison. This may result in members of the intervention group discussing content of BFO with control group participants, which may contaminate the outcomes and violate the stable unit treatment value assumption. However, this study has to be conducted in a very specific kind of prison environment, which limited the number of potential research sites and made the option of randomization at the level of the research site impractical. Indeed, recruiting prisons to participate in research is difficult generally, given the unique challenges faced within such secure environments and the additional challenges posed by issues such as understaffing in most UK prisons – this makes it difficult for prisons to participate in additional activities outside of the core prison regime. And from a methodological perspective, the study has to be conducted in an open prison where participants may conceivably have an opportunity to continue to use substances, although the authors note there is still significant illicit substance use in the UK and other countries, even in high-secure prisons.

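### One practitioner team, all trained in BFO, treats both arms; separating the standard-treatment groups keeps participants apart but not staff, so BFO-specific content could reach controls through staff, to an unknown and possibly small extent

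*Protocol article*

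**What the plan says.** **Who delivers treatment.** Protocol article, Procedure: "Practitioners will be responsible for delivering both BFO and the standard treatments received by the two study groups". On training, the same section says: "The site investigators have trained all participating practitioners in delivering BFO as CAT and have also conducted training around RCT methodology". No group of staff without BFO training is described for the control arm.

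**The safeguard.** Under Standard treatment, a measure is introduced with the words "In order to avoid violation of the stable unit treatment value assumption". The measure is that "participants in the BFO group will receive their group-based standard treatment in groups that are run separately from the group-based standard treatments the control group" receives. It applies to group-based standard treatment. The same section also describes one-to-one CBT-based therapy, usually given by specialist therapists, and Procedure describes weekly key-working for all offenders as part of standard treatment.

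**The record.** Standard treatment lists what is collected: which treatments each man received, "the number of sessions completed, what kind of practitioner has delivered it", and medication. It refers to Appendix B, which is not shown.

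**The digital barrier.** Controls complete their assessments on a separate platform, "without providing access to any of the digital intervention content provided by BFO" (Procedure). BFO itself needs an access code and a personal account.

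**The acknowledged limitation.** The Discussion says of individual randomization: "This may result in members of the intervention group discussing content of BFO with control group participants". It adds that this could contaminate outcomes and breach the stable unit treatment value assumption (SUTVA). Transfer through staff is not mentioned.

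**The concern.** The authors set out to protect the contrast between arms, and they chose a measure aimed at one route only, contact between participants. A second route runs through staff. A practitioner who has been trained in BFO, and may be leading BFO sessions, could bring its framing, its Lifestyle Balance Model diagram or its named exercises into a control-arm group, a key-working session or one-to-one work. Keeping the men in different rooms does not affect this.

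If it happened, control outcomes would move toward those of the BFO arm and the estimated difference would shrink. The bias is toward no effect, so it would not create a false benefit. The cost is in interpretation: after a null or weak result, readers would want to know whether controls had met BFO content, and the record as the article describes it names nothing about session content. That information can only be collected while treatment is being delivered or soon after.

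**Working it through.** **Step 1: which routes the safeguard covers.** The sections set side by side:

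| Contact of a control participant | Covered by separate groups? | Named as a limitation? |
|---|---|---|
| BFO participants within group-based standard treatment | Yes | Yes (Discussion) |
| BFO participants elsewhere in the prison | No | Yes (Discussion) |
| BFO-trained facilitator of a control standard-treatment group | No | No |
| BFO-trained practitioner in weekly key-working | No | No |
| Practitioner giving one-to-one therapy, if BFO-trained | No | No |
| BFO software | Not relevant; blocked by access code and separate platform | Not needed |

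The three staff rows are neither covered nor named.

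**Step 2: the plan's own sample-size figure.** Inputs from Power calculation: 120 evaluable, 50% attrition. 120 / (1 − 0.50) = 240, which matches the stated 240. The 60 per group cannot be reproduced, because no effect size or standard deviation is given.

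**Step 3: the effect implied by 60 per group.** Inputs: power 0.80 and α = .05 from Power calculation. Two-sided testing is my assumption. With a normal approximation for two means,

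d = (1.960 + 0.842) × √(2/60) = 2.802 × 0.1826 = 0.511.

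**Step 4: what leakage would do.** Suppose controls gain a share c of the BFO effect. The observable difference becomes (1 − c) × d. Power is then Φ(2.802 × (1 − c) − 1.960), and the number per group needed to restore 80% is 60 / (1 − c)².

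| c (assumed) | Remaining d | Power at 60 per group | N per group for 80% |
|---|---|---|---|
| 0% | 0.511 | 0.80 | 60 |
| 5% | 0.486 | 0.76 | 67 |
| 10% | 0.460 | 0.71 | 75 |
| 20% | 0.409 | 0.61 | 94 |
| 30% | 0.358 | 0.50 | 123 |

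A t-test version, which starts from d = 0.516, gives the same power to two decimals at 10%, 20% and 30%. The table shows how power responds to dilution. It says nothing about how much dilution to expect here. The planned analysis is a repeated-measures ANCOVA with a distribution such as Poisson, not a two-sample comparison of means.

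**The case against.** The case on the other side is substantial.

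- **A reader might infer that each practitioner works in both arms.** The text does not say so. It gives both tasks to practitioners as a team, as distinct from site investigators. Standard groups are usually led by key-workers and formal therapy by specialists, so some division of labour may exist. This stands, and the point is therefore about a shared team with no stated separation.
- **A reader might infer that BFO itself could leak.** Most of it could not. The content is computer-delivered, entry is controlled, and tailoring is done by the program from each user's own scores. What staff could pass on is technique, framing and named materials. This stands and limits the likely size.
- **A reader might count any use of urge surfing or mind-trap work with a control as contamination.** Table 1 traces these to general CBT, mindfulness and relapse-prevention approaches. Standard treatment already includes CBT-based work, and staff were experienced before the trial. A control who meets such a technique may simply be receiving the intended comparator. This stands, and any measure of exposure must ask about content specific to BFO.
- **A reader might infer that the treatment record cannot reveal leakage.** Appendix B is not shown and could hold more than the article lists. The RCT training might also have covered the issue. Both are possible, and the article confirms neither.
- **Contamination is already disclosed.** The Discussion concedes a possible SUTVA breach and explains why randomizing by prison was impractical. Sharing staff is a usual result of individual randomization at one site. But the disclosure names only conversation between participants.

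What survives is narrow. The stated safeguard and the stated limitation both omit the staff route, and the Procedure section is what opens it.

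**Conclusion.** The point holds in a limited form. One BFO-trained team serves both arms. The separate groups keep participants apart but not facilitators, they leave out key-working and one-to-one therapy, and the limitation names only transfer between participants. BFO-specific content could reach controls through staff and bias the difference toward zero.

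The size cannot be derived from the documents and may be small. The power figures of about 71%, 61% and 50% rest on an assumed leakage of 10%, 20% and 30%, a back-solved effect of about 0.51, and a simple two-sided comparison. They do not show that the trial is underpowered or that contamination will occur. The documents also do not support saying that leakage would be undetectable, since Appendix B has not been seen. The practical case for change is that a few inexpensive items would help readers interpret a null result.

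**What to change.** 1. Instruct practitioners not to use BFO-specific materials in control-arm sessions: program content, the Lifestyle Balance Model and strategies under their BFO names. Apply this to groups, key-working and one-to-one sessions. Generic CBT or relapse-prevention work that belongs to standard treatment is unaffected.
2. Add a code for the individual practitioner to the existing standard-treatment record, if Appendix B does not already have one.
3. At the existing 4-week assessment, ask each control participant whether BFO-specific content was shown to or discussed with him, and whether by staff or by another participant.
4. Report exposure in the control arm alongside the ITT result, leaving the ITT analysis unchanged, and name the staff route with the contamination limitation in the Discussion.

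Rostering so that whoever leads BFO in a 4-week wave does not lead control groups in that wave is optional where staffing allows. It is not a full remedy. All practitioners are already trained in BFO, rotation would bring recent BFO leaders into control groups, key-working is left out, and the Discussion reports understaffing in most UK prisons. A tick box for any BFO strategy used is not advised, because it could not separate leakage from usual care.

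The cost is a short instruction, one form field and one question. The answers will carry some self-report error.
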